### 2.4 Sample size, randomization and blinding

#### 2.4.1 Sample size calculation

The primary outcome for this study is the change in the COPD Assessment Test (CAT) scores before (week 0) and after (week 12) the intervention. Sample size calculation is based on the results of our pilot trial, which showed a mean change in CAT scores of 5.0 for patients in the acupuncture group and 1.4 in the sham acupuncture group. Using a two-tailed test with type I error of 0.05 and power of 80%, a sample size of 32 cases per group is calculated with a maximum of 10% of participants allowed to drop out or disengage, for a required sample size of 36 cases per group, and a total of 72 participants will be included. Furthermore, 36 healthy participants will be included. The sample size calculation was completed in PASS 15.0 with One-Way Analysis of Variance (ANOVA) F-Tests module.

#### 2.4.2 Randomization and allocation concealment

COPD patients will be randomly divided into MA and SA groups according to a random number table generated by computer. The random sequences will be sealed in light-tight envelopes, which will be opened only when eligible participants are enrolled. Generation and allocation of the random sequences will be performed independently by a research assistant (RA) not be involved in the treatment and outcome assessment.

#### 2.4.3 Blinding

Patients, outcome assessors, data entry clerks and statistical analysts will be blinded. Letters A and B will be used instead of specific group names, and the same manipulation device will be applied to mask the difference in acupuncture between the two treatment groups of patients. During treatment, patients will be arranged to be in different rooms to avoid communication. The investigators, therapists, efficacy assessors and data statisticians will be separated throughout the whole study process. At the end of the 12-week treatment, patients will be asked if they received traditional acupuncture (yes, no, or unclear) to determine if the blinding was successful.

### 2.5 Intervention and comparison

#### 2.5.1 Patients with COPD

Details of the acupuncture intervention are reported based on the STRICTA check list in Table 3. According to the results of the existing literature collation and expert consultation, 7 pairs of acupoints are screened for treatment, including: Zhongfu (LU1), Feishu (BL13), Pishu (BL20), Shenshu (BL23), Zusanli (ST36), Fenglong (ST40), and Dingchuan (EX-B1). All acupoints are taken bilaterally, and the number of needles inserted is 7 × 2, for a total of 14 acupoints (needles). Details of each acupoint are shown in Table 4 and Figure 2. The acupuncture device same in appearance will be applicated uniformly for both MA and SA group. A rubber cushion is designed to be attached to each acupoint, and acupuncturists will operate through the cushion so that patients or bystanders cannot tell whether the needles are actually inserted or not (Figure 3). Each sub-center will be assigned an acupuncturist responsible for the treatment of all patients within that center. Acupuncturists are required to be licensed with at least 3 years of clinical experience. The expected and actual number of treatments for each patient will be recorded for assessing patient compliance.

**TABLE 3 T3:** STRICTA checklist.

Item	Item number	Detail
1. Acupuncture rationale	(1a) Style of acupuncture	Traditional Chinese medicine
	(1b) Reasoning for treatment provided, based on historical context, literature sources, and/or consensus methods, with references where appropriate	Acupuncture treatment based on the theory of TCM, literature sources, and clinical experience in acupuncture and COPD
	(1c) Extent to which treatment was varied	Standardized acupuncture treatment
2. Details of needling	(2a) Number of needle insertions per subject per session (mean and range where relevant)	14
	(2b) Names (or location if no standard name) of points used (uni/bilateral)	Zhongfu (LU 1), Feishu (BL 13), Pishu (BL 20), Shenshu (BL 23), Zusanli (ST 36), Fenglong (ST 40), Dingchuan (EX-B1) All points will be taken bilaterally.
	(2c) Depth of insertion, based on a specified unit of measurement, or a particular tissue level	From 10 to 30 mm
	(2d) Response sought (e.g., de qi or muscle twitch response)	The “de qi” sensation will be achieved by lifting and thrusting combined with twirling and rotating the needles.
	(2e) Needle stimulation (e.g., manual, electrical)	Manual acupuncture
	(2f) Needle retention time	30 min
	(2g) Needle type (diameter, length, and manufacturer or material)	Sterile, disposable stainless acupuncture needle, 0.25 mm × 40 mm (Hwatuo, Suzhou Medical Co. Ltd., Jiangsu, China).
3. Treatment regimen	(3a) Number of treatment sessions	36 treatment sessions in acupuncture groups.
	(3b) Frequency and duration of treatment sessions	3 times a week, 30 min for each session.
4. Other components of treatment	(4a) Details of other interventions administered to the acupuncture group (e.g., moxibustion, cupping, herbs, exercises, lifestyle advice)	The standard treatment of COPD is based on the *Global Strategy for the Diagnosis, Management, and Prevention of Chronic Obstructive Lung Disease: the GOLD science committee report 2022*.
	(4b) Setting and context of treatment, including instructions to practitioners and information and explanations to patients.	The trial will be conducted in four sub-centers, all of which are the highest level hospitals in the Mainland Chinese healthcare system. All information and explanations will be provided to participants.
5. Practitioner background	(5) Description of participating acupuncturists (qualification or professional affiliation, years in acupuncture practice, other relevant experience)	All acupuncturists are qualified Chinese medicine practitioners with a degree in acupuncture and at least 3 years of clinical experience, and training in standard operating procedures for acupuncture in COPD.
6. Control or comparator interventions	(6a) Rationale for the control or comparator in the context of the research question, with sources that justify this choice	Sham acupuncture is chosen as the control group to reflect the effect of acupuncture-assisted treatment of COPD as much as possible.
	(6b) Precise description of the control or comparator. If sham acupuncture or any other type of acupuncture-like control is used, provide details on items 1 to 3 above.	The SA group will use the same acupuncture points, operating rituals and procedures as the MA group, as well as the same appearance of the needling device. However, the actual needles used are flat needles that will not pierce the skin and generate the de-qi sensation.

TCM, traditional Chinese medicine; COPD, chronic obstructive pulmonary disease; SA, sham acupuncture; MA, manual acupuncture.

**TABLE 4 T4:** Locations of acupoints.

Acupoints	Locations
Zhongfu (LU 1)	On the upper lateral chest, 6 cun from the middle of the chest, level in the first intercostal space.
Dingchuan (EX-B1)	0.5 cun lateral to DU 14.
Feishu (BL 13)	1.5 cun lateral to the depression below the spinous process of the 3th thoracic vertebra.
Pishu (BL 20)	1.5 cun lateral to the depression below the spinous process of the 11th thoracic vertebra.
Shenshu (BL 23)	1.5 cun lateral to the depression below the spinous process of the 2th lumbar vertebra.
Zusanli (ST 36)	3 cun directly below ST 35, and one finger-breadth lateral to the anterior border of the tibia.
Fenglong (ST 40)	One finger-breadth lateral to ST 38, and at the midpoint of the line joining ST 35 and the tip of the external malleolus.

**FIGURE 2 F2:**
[figure not shown]
Locations of acupoints.

**FIGURE 3 F3:**
[figure not shown]
The diagram of acupuncture devices. **(A)** Acupuncture; **(B)** Sham Acupuncture. ① Needle handle; ② Needle body; ③ Rubber cushion; ④ Blunt-tipped sham needle; ⑤ skin; ⑥ Real needle point.

##### 2.5.1.1 Manual acupuncture (MA) group

Patients in the MA group will choose a prone treatment position. After skin disinfection, the acupuncturist will insert the needle into the acupoint through the rubber base adhered to the acupoint. The direction and angle of acupuncture will be strictly under the basic requirements of acupuncture operation. 0.5-cun acupuncture needles (0.25 × 13 mm, Hwato, Suzhou, China) will be used to insert in a depth of 10–15 mm for the BL13. 1-cun acupuncture needles (0.25 mm × 25 mm, Hwato, Suzhou, China) will be used to insert in a depth of 15–20 mm for the EX-B1, LU1, and BL20. 1.5-cun acupuncture needles (0.25 mm × 40 mm, Hwato, Suzhou, China) will be used to insert in a depth of 25–30 mm for the BL23, ST36, and ST40. After needle insertion, a modest twisting and lifting maneuver will be performed to obtain a sensation of *deqi* (soreness, numbness, distension or heaviness) (44). The degree of *deqi* sensation will be assessed immediately after the patient having *deqi* sensation (45). The needles will be retained for 30 min each time, and *deqi* sensation operation will be performed every 10 min for 15 s each time. Treatments will be given 3 times per week (1–2 days apart) for a total of 12 weeks.

##### 2.5.1.2 Sham acupuncture (SA) group

The SA group will select the same acupoints and treatment position as the MA group. The acupuncturist will applicate a special 0.5-cun flat-tipped needle (0.3 mm × 0.13 mm) to puncture vertically into the base of the rubber cushion so that the body of needle can be fixed on the patient’s skin surface. The blunt needles can make patients feel the pain without puncturing their skin. The duration of needle retention is the same as that of the MA group (30 min). A manipulation ritual of twisting and lifting like the MA group will be performed after fake insertion and every 10 min during the retention period, but without producing a *deqi* sensation, to simulate real treatment as far as possible. Equally, the intervention will be taken 3 times per week (1–2 days apart) for a total of 12 weeks. Considering the ethical requirements, patients in SA group will receive free compensatory acupuncture treatment at the end of the trial.

##### 2.5.1.3 Basic treatment and medication changes

During the baseline period, all details of medications used by the patients to treat COPD and other underlying conditions will be recorded on a case report form (CRF), including the name of the medication, the dosage used, the frequency of use, the route of administration, and when the medications begin and end. Any changes in the patient’s medications throughout the study period will also be recorded in detail. If the patient experiences an acute exacerbation, the possibility of continuing acupuncture treatment will be assessed by a respiratory medicine specialist. If an acute exacerbation occurs that necessitates the application of antibiotics or hospitalization to control the infection, the trial will be discontinued and the time and reason for being discontinued will be recorded by the investigators.

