### 2.6 Outcome measurements

#### 2.6.1 Primary outcome

COPD Assessment Test (CAT) The change in the CAT scores before (week 0) and after (week 12) the intervention is chosen as the primary outcome.

The scale evaluates and reflects the severity of COPD patients’ conditions through 8 items, including 3 indicators of clinical symptoms: cough, sputum, and chest tightness, 2 indicators of tolerance: exercise tolerance, daily activities (status of limited activities at home), and 3 indicators of life quality: sleep quality, energy, and mood (confidence in outings). The response values of each item are ranging from 0 to 5 (0 = no impairment). Response values for all 8 items will be summed up to obtain the total scores of (ranging from 0 to 40). Higher scores indicate a greater impact of the disease on the patient’s health and life (46): 0–9 is considered a low impact, 10–20 is considered a moderate impact, 21–30 is considered a high impact, and 31–40 is considered a very high impact (47). In addition, week 4, week 8 and the follow-up period (week 38, week 64) will also collect data on this scale’s scores (Table 1).

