(4) Number of moderate or severe acute exacerbations of during the follow-up period: The number of moderate or severe acute exacerbations in the follow-up period will be counted, as one of the indicators for assessing the long-term effects of acupuncture-assisted treatment for COPD.

The moderate (patient needs to be treated with short acting bronchodilators plus antibiotics and/or oral corticosteroids) and severe (patient requires hospitalization or visits the emergency room) acute exacerbations of COPD are defined and classified referring to the *Global Strategy for the Diagnosis, Management, and Prevention of Chronic Obstructive Lung Disease: the GOLD science committee report 2022* (41).

The measurement nodes for the outcome indicators above are detailed in Table 1.

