### 2.7 Safety assessment

Safety will be assessed by vital signs examination and routine blood tests before and after the treatment period. Adverse events (AEs) associated with the intervention, including bleeding, hematoma, needle breakage, local infection, persistent pain, syncope, etc., must be reported promptly and recorded in the CRFs, which included symptoms, signs, time of occurrence, extent, duration, disposal measures, process and results of AEs (Note: acute exacerbation of COPD is not counted as an adverse event). Serious cases should to be reported to the Project Management Office and Ethics Committee of Chengdu University of Traditional Chinese Medicine within 24 h and their participation in trial will be aborted. Upon occurrence of an adverse event, participants will immediately receive appropriate treatment and decide whether to withdraw from the trial at their own discretion. Participants who abort the trial will continue to be investigated and followed up, and the results will be recorded accordingly.

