### 2.10 Statistical analysis

Analyses of effectiveness, indicators of DNA library of gut microbiota, content of metabolites, percentage of immune cell and expression levels of inflammatory cytokines will be performed according to the Per Protocol Set (PPS) principle. The missing data will be filled in by multiple interpolation. SPSS 27.0 software (IBM Corp, New York) will be applied for statistical analysis. Quantitative indicators will be described by mean value (± standard deviation) or median (± interquartile range), and classification indicators by frequency and percentage. Baseline data will be analyzed using Chi-square or Fisher precision tests (data with frequency less than 5) and ANOVA. Sensitivity analyses will be performed using ANOVA.

The outcome of effectiveness, indicators of DNA library of gut microbiota, content of metabolites, percentage of immune cell and expression levels of inflammatory cytokines will be analyzed by linear mixed effects model. Fixed effects will be set for analyzing groups, COPD subtypes and smoking index (calculation method: smoking years × daily smoking number ÷20); Random effects for sub-centers and baseline outcome measures, both including intercept; Model-based covariance will be applied to test the fixed effects and coefficients, the degree of freedom will use residual method, and the maximum number of iterations will be set to 100. To control for type I error rates under multiple comparisons, the Benjamini–Hochberg method will be utilized for multiple comparison correction. Multiple linear regression will be used to analyze the relationship between clinical efficacy and gut microbiota, metabolites, immune cells and inflammatory factors. Statistical tests will be bilateral with *P* < 0.05 considered statistically significant.

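### Effectiveness is analysed only on the Per Protocol Set while a serious exacerbation ends participation, so patients who worsen may drop out of the CAT and exacerbation results, and exacerbations in weeks 0-12 are never compared by arm

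*Protocol article*

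**What the plan says.** Section 2.5.1.3 deals with exacerbations in two steps. In general, "the possibility of continuing acupuncture treatment will be assessed by a respiratory medicine specialist". For the more serious ones the wording changes: "If an acute exacerbation occurs that necessitates the application of antibiotics or hospitalization to control the infection, the trial will be discontinued", with the time and reason recorded.

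Section 2.10 states that the analyses of effectiveness and of the laboratory outcomes "will be performed according to the Per Protocol Set (PPS) principle". It adds: "The missing data will be filled in by multiple interpolation". No intention-to-treat or full analysis set is named anywhere in the article. The one sensitivity analysis mentioned names a method (ANOVA) and no second analysis set.

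Two clinical outcomes are affected:
- Primary (section 2.6.1): "The change in the CAT scores before (week 0) and after (week 12) the intervention is chosen as the primary outcome".
- Secondary (section 2.6.2.1, item 4): "The number of moderate or severe acute exacerbations in the follow-up period will be counted". The Discussion confirms that this means the year after treatment ends, and Table 1 schedules the exacerbation count only at weeks 38 and 64.

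Section 2.7 contains two relevant statements. One is a note that "acute exacerbation of COPD is not counted as an adverse event". The other is "Participants who abort the trial will continue to be investigated and followed up".

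**The concern.** The event that triggers discontinuation is itself an outcome. Section 2.6.2.1 defines moderate and severe exacerbations largely by antibiotics, oral corticosteroids, emergency visits and admission, so the exit rule overlaps heavily with the secondary endpoint. It is also likely to go with a worse week-12 CAT. Exclusion on this ground depends on how the patient is doing, and its frequency can differ by arm. If more sham patients exit, the Per Protocol Set understates the CAT benefit. If more needled patients exit, it overstates it.

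The second issue does not depend on how the exit rule is read. Exacerbations are kept out of the adverse events, and the exacerbation outcome starts only after week 12. An excess of moderate or severe exacerbations during needling would therefore enter neither the planned outcome count nor the adverse events, although section 2.1 makes safety an objective.

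Stopping at antibiotic use is sensible for the week-12 stool sample (section 2.6.2.2). It is no reason to remove the patient from CAT or from the exacerbation count.

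**Working it through.** **Inputs from the article (section 2.4.1).** 32 per group, 10% dropout, 36 per group; mean CAT changes 5.0 and 1.4, so a difference of 3.6; two-sided 0.05; 80% power. Treatment lasts 12 weeks, so t = 12/52 = 0.231 years.

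**Inputs assumed, because the article gives none.** r = 0.5 or 1.0 exacerbations per patient-year; s = 0.5 or 1, the share that triggers the rule.

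**The plan's own figure.** 32/0.9 = 35.6, rounded up to 36 per group, 72 in all. This reproduces. No SD is stated. A two-sample t-test with 32 per group, 80% power and a difference of 3.6 implies SD = 5.06, a standardised difference of 0.711.

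**Share of patients with a trigger in weeks 0-12.** Poisson: 1 - exp(-s·r·t). Gamma frailty with shape 1: 1 - 1/(1 + s·r·t).

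| r | s | Poisson | Per 36 | Frailty |
|---|---|---|---|---|
| 0.5 | 0.5 | 0.056 | 2.0 | 0.055 |
| 0.5 | 1 | 0.109 | 3.9 | 0.103 |
| 1.0 | 0.5 | 0.109 | 3.9 | 0.103 |
| 1.0 | 1 | 0.206 | 7.4 | 0.188 |

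Eligibility shifts these figures. Let L(u) = 1/(1 + r·u) and a = 0.25·s + (4/52)·(1 - s), the trigger-free time implied by no antibiotics for 3 months and no exacerbation for 4 weeks.
- Stability criteria only, 1 - L(a + s·t)/L(a): 0.051, 0.093, 0.090, 0.156.
- Adding an event in the past year, which Table 2 requires but the text list in section 2.3.2.1 omits, 1 - [L(a + s·t) - L(1 + s·t)]/[L(a) - L(1)]: 0.086, 0.158, 0.140, 0.243.

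Only a range is supportable: about 5-20%, or 9-24% if Table 2 governs.

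**Power at SD 5.06.**
- Exits on top of the 10% allowance: 32 × 0.95 = 30.4 and 32 × 0.80 = 25.6. Rounded down, n = 30 gives 77% and n = 25 gives 69%; n = 26 would give 71%.
- Exits absorbed by the allowance: 36 × (1 - 0.109) = 32.1 gives 80%; 36 × (1 - 0.206) = 28.6, taken as 28, gives 74%.

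**CAT bias.** If exiting patients improve D points less than the others in both arms, the Per Protocol difference minus the all-randomised difference equals D × (exit share MA - exit share SA).
- D = 2, gap 0.05: 0.1 points.
- D = 4, gap 0.05 or 0.10: 0.2 or 0.4 points.
- D = 6, gap 0.10: 0.6 points.
- Equal exits: zero.

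If D differs by arm, the shift is (D in MA × exit share MA) - (D in SA × exit share SA). Suppose every exiting patient has a change of 0, so D is 5.0 in MA and 1.4 in SA. Equal 10% exits then give 0.50 - 0.14 = 0.36, so the all-randomised difference is 3.24. A harsher case, 30% against 10% exits with a change of -3 (D = 8.0 and 4.4), gives 2.40 - 0.44 = 1.96, so 1.64 remains.

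**Exacerbation ratio when every week 0-12 exit is excluded (frailty model, treatment-phase ratio 0.7).**
- True follow-up ratio 0.70: 0.7·(1 + s·r·t)/(1 + 0.7·s·r·t) = 0.712, 0.722, 0.722, 0.742.
- True follow-up ratio 1.00, with an effect only during treatment: (1 + s·r·t)/(1 + 0.7·s·r·t) = 1.017, 1.032, 1.032, 1.060.

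Under a homogeneous Poisson model both shifts are zero.

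**The case against.** The strongest reply is that nothing in the article says an exacerbating patient leaves the analysis. Per Protocol membership is undefined, which an article may leave to the full protocol. The quoted sentence follows one about continuing acupuncture, so it may mean only that treatment stops. Section 2.7 promises continued follow-up of those who abort, and planned imputation suggests that incomplete patients are meant to be kept. This stands in so far as the loss is a risk and not a certainty. It does not remove the risk: follow-up data need not enter a per-protocol analysis, and imputation reaches only patients kept in the set.

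The quantification can also be challenged. Exacerbation exits may be part of what the 10% allowance covers, in which case power is 80% to 74% rather than 77% to 69%. The shift in the exacerbation ratio comes entirely from assumed frailty. The zero CAT bias at equal exits needs the same D in both arms. All three points are correct, and they are reasons to read the figures as illustrations.

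Finally, safety tables are normally left to an analysis plan, and section 2.5.1.3 records medication changes and discontinuations, so most of the data will exist. Keeping disease events out of the adverse events is also a common choice. But here that exclusion combines with an outcome window that starts only after week 12, so the gap follows from stated rules rather than from omitted detail.

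**Conclusion.** The concern holds. A superiority comparison against sham should not rest on a Per Protocol Set alone, least of all when the exit rule is close to a secondary endpoint. That patients will leave the CAT and exacerbation analyses is a risk that depends on an undefined set. That weeks 0-12 exacerbations have no planned by-arm comparison follows from the article as written.

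Under the assumed 0.5 to 1.0 events per year, 2 to 7 of 36 patients per arm are exposed, against the 4 per arm that the dropout allowance covers. Both biases are modest under the main assumptions: the CAT shift is 0.1 to 0.6 points of 3.6 and can run in either direction, and a ratio of 0.70 appears as 0.71 to 0.74. The CAT bias becomes large only with a wide imbalance in exits. The lost patients and the absent treatment-phase safety comparison are the weightier consequences. This should be fixed; confidence in the size is medium, because every event rate is assumed.

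**What to change.** - **Section 2.5.1.3:** state that such an exacerbation stops or pauses acupuncture only, and that all randomised patients stay in scheduled assessments to week 64.
- **Section 2.10:** make the all-randomised set the main analysis for the CAT change and the exacerbation count, with the Per Protocol Set as supportive. Antibiotic-exposed patients may be handled separately for the microbiota outcome.
- **Table 1 and CRF:** record exacerbations at weeks 4, 8 and 12 as well as at weeks 38 and 64.
- **Section 2.7:** tabulate moderate or severe exacerbations and hospitalisations in weeks 0-12 by arm as safety data.
- **Section 2.6.2.1, item 4:** keep the week 12-64 count and report the week 0-64 count beside it.

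The cost is protocol wording, one CRF entry at three visits that already take place, and one extra table.
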